**Conclusions:**

This study tests a novel digital health intervention integrated into trusted care systems. If effective, the Connected for Wellness mobile app may serve as a scalable strategy to reduce disparities in mental health care access and engagement for youth across the United States.

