## Introduction

### Background

Could a mobile mental health app designed for youth and caregivers help address mental health service barriers? For decades, research has documented the ongoing and persistent inequities in mental health care access for many populations, including both rural and urban [1-3]. Innovative aspects of the clinical trial protocol reported in this paper include using a mobile app codeveloped with youth and families through participatory informatics to drive technological innovation considering youth and caregiver priorities regarding customizable features and in-app resources.

Our previous work supports the hypothesis that mobile apps and other digital health interventions are effective for delivering mental health and prevention services provided that they meet the needs and preferences of end users [4]. These interventions can be successfully implemented within child-, adolescent-, and family-serving systems of care. Unlike clinicians’ time, technology offers a nonconsumable strategy (ie, available asynchronous content vs scheduled therapist time) for improving mental health care access [5]. The United States has witnessed an increasing need for youth mental health services, especially for stress-related challenges [6,7] and populations disproportionately affected [8]. National data reveal that, after controlling for sociodemographics, severity of symptoms, income, and health insurance, Black and Latino youth with similar needs as White youth were almost half as likely to receive mental health services [3].

Barriers to care exist across multiple levels, including cultural, community, family, and systemic factors. For instance, Latino caregivers may perceive children’s behavioral challenges as issues to address within the family, struggle with the lack of linguistically and culturally appropriate services, or experience stigma and perceptions of mental health needs that differ from those of mental health care providers [9]. Rural communities of all backgrounds are also underserved. These systematic factors contribute to reduced use of mental health services even in high-risk populations, underscoring the need for focused interventions that can both help mental health symptoms and risks and promote and facilitate engagement with services [10].

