### Primary Outcomes: Cascade-of-Care Framework

The primary study outcomes are based on the cascade-of-care framework that focuses on population-level health needs and tracks individuals across relevant stages of a health care continuum [37,38]. Originally developed by the Juvenile Justice–Translational Research on Interventions for Adolescents in the Legal System [39,40], the steps in the cascade of care are identification of a behavioral health need, referral to behavioral health care, initiation of services, and engagement with services (>3 visits). The cascade of care has been adapted for youth in foster care [41]; this version was used for this study. Data on each step of the cascade of care will be obtained from deidentified electronic medical records and administrative data at the individual youth level from each of the study sites. This approach, which uses established databases, will enable comparison of cascade-of-care outcomes after implementation to data that were collected before preimplementation years. As detailed in the analytic plan in the Data Analysis section, individual-level data will be aggregated to the site level to test the hypothesis that implementation of the Connected for Wellness mobile app intervention is associated with improvements in youth progression through the cascade of care compared to the (preintervention) control condition. Improvements in the cascade of care are an established public health outcome as they help identify gaps in care and assess the effectiveness of the mobile app intervention. At a population level, in schools or primary care clinics, examining the cascade can inform how well an intervention improves youth access, engagement, and outcomes for a specific population and whether the intervention effectively addresses their unique needs and disparities. Statistical power was determined relative to the current level of each of the cascade outcomes (identification of mental health need, match to services, and initiation of services) in the sites as reflected in administrative data. Power was calculated separately for each cascade outcome. With a power of 0.8, an α value of .05, and 2-tailed tests, the planned design and sample sizes enable detection of small differences between the intervention and control conditions in all the cascade outcomes (2%-10%). Table 2 shows the operational definitions for the cascade-of-care outcome variables, and Table 3 shows the definitions, data collection, and outcomes.

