**Table 2 table2:** Cascade-of-care model based on Connected for Wellness triage outcomes.

Step	Rate	Operational definition
Youth at site (step a)	(a)	Total number of youth enrolled at a high school campus or on a patient panel at the primary care clinic site
Need identified (step b)	(b/a)	Subset of total enrolled youth (step a) who complete mental health and social determinant of health needs identification at school or the primary care clinic
Matched to services (step c)	(c/b)	Subset of youth with needs (step b) who receive a referral
Initiated services (step d)	(d/c)	Subset of those referred to services (step c) who initiate services (eg, first treatment session)
Engaged in services (step e)	(e/d)	Subset of those who initiate services (step d) who have ongoing sessions (≥3 visits)

**Table 3 table3:** Primary outcomes based on the cascade-of-care framework and covariates for generalized linear mixed model (GLMM) analysis.

Cascade step	Operational definition and data description	Covariates in GLMM
Need identified	Youth who completed self-assessments or were flagged by navigators	Age, gender, race, ethnicity, site type (school vs clinic), and urban or rural
Matched to services	Referral documented in site records or follow-up logs	All the aforementioned covariates+previous mental health history if available
Initiated services	Attended first mental health appointment	Same as the previous covariates
Engaged in services	≥3 treatment sessions attended	Same as the previous covariates+time since app onboarding

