The GLMM models will include county and intervention (vs control) as fixed effects, with site and youth as random effects. Study month will be treated as a continuous variable to account for potential secular trends. The primary focus will be on the intervention effect. For youth with mental health need, we will also examine time-to-event outcomes (eg, days to service initiation) using Poisson models with a log link function. If overdispersion is detected, we will use a negative binomial model. The relative risk ratio for intervention will indicate whether the app reduces time to service matching and initiation. To address heterogeneity, the GLMM will include random intercepts for sites and fixed effects for county and wave. We will test for interactions between intervention status and site characteristics (eg, urban vs rural and school vs clinic). We will also conduct stratified analyses by key demographic variables (race and ethnicity, age, and gender) to explore subgroup effects.

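### Race and ethnicity, age and gender are examined only by stratified analyses, so no planned analysis estimates whether the app's effect differs between demographic groups

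*Protocol article*

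**What the plan says.** All references are to the protocol article.

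- **Data Analysis, site factors:** "We will test for interactions between intervention status and site characteristics (eg, urban vs rural and school vs clinic").
- **Data Analysis, next sentence, demographic factors:** "We will also conduct stratified analyses by key demographic variables (race and ethnicity, age, and gender) to explore subgroup effects".
- **Table 3:** the GLMM covariates for the first cascade step are "Age, gender, race, ethnicity, site type (school vs clinic), and urban or rural", and the later steps build on that list. These are adjustment terms. No intervention-by-demographic term is listed.
- **Links to disparities:** the Background cites national data that "Black and Latino youth with similar needs as White youth were almost half as likely to receive mental health services". The outcomes section says the cascade can inform "whether the intervention effectively addresses their unique needs and disparities". The abstract's Conclusions say that, if effective, the app "may serve as a scalable strategy to reduce disparities in mental health care access and engagement for youth across the United States". Expected Findings cites an earlier review's call for larger trials that look at subgroup differences and says the study aims to address such gaps.
- **Status of the subgroup work:** it is labelled as exploring, the main focus is the overall intervention effect, and no disparity contrast is among the primary hypotheses.

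**The concern.** Whether an intervention works differently in two groups is a question about the difference between two effects. A stratified analysis gives one effect per group and leaves that difference unestimated unless a further contrast is specified, and none is. The article names the suitable tool, an interaction in the same GLMM, and assigns it to site factors only.

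Two things are at stake. First, a pattern of significance in one group and not in another tends to be read as a differential effect, although it arises readily when the true effects are equal. Second, if the app does help one group more than another, no planned estimate or interval would show it. The strata also come from the same 20 sites, so their estimates are not independent, and comparing separate fits after the event ignores that shared error.

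**Working it through.** **The plan's own figure.** The article states power 0.8 at two-sided .05 for differences of 2%-10%, for the overall effect. This cannot be reproduced, because no baseline rates, numbers of youth, intracluster correlation or period structure are given. The check uses only what 80% power at two-sided .05 implies: an overall noncentrality of 1.960 + 0.842 = 2.802.

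**Assumptions not in the article.** The true effect is the same in every stratum. Stratum shares are assumed. A share s of the variance of the overall effect estimate lies at site level and is common to all strata; the rest belongs to each stratum.

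**1. Independent strata (s = 0).** A stratum holding a fraction f of the information has noncentrality 2.802 × √f.

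| Split | Power in each stratum | Exactly one significant |
|---|---|---|
| 50:50 | 0.51, 0.51 | 2 × 0.51 × 0.49 = 50% |
| 70:30 | 0.65, 0.34 | 55% |
| 80:20 | 0.71, 0.24 | 61% |

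For k equal strata with power p each, the chance of a mixed pattern is 1 − p^k − (1 − p)^k. This gives 70% for k = 3 (p = 0.37) and 74% for k = 4 (p = 0.29). Even two independent strata with 80% power each disagree 2 × 0.8 × 0.2 = 32% of the time.

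**2. Shared site-level error (s > 0).** With the overall variance set to 1, each of k equal strata has variance s + (1 − s)k, noncentrality 2.802 / √[s + (1 − s)k], and pairwise correlation s / [s + (1 − s)k]. For k = 2 and s = 0.5 the variance is 1.5, the noncentrality 2.29, the power 0.63 and the correlation 0.33. Simulated chance of a mixed pattern:

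| Strata | s = 0 | s = 0.5 | s = 0.8 |
|---|---|---|---|
| 2 | 50% | 37% | 22% |
| 3 | 70% | 63% | 42% |
| 4 | 74% | 76% | 58% |

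Shared error lowers the two-stratum figure but does not remove the problem. With four strata a mixed pattern remains more likely than not.

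**3. What an interaction test offers.** When effects are equal, it has a 5% false-positive rate per test. Three factors by four cascade outcomes is 12 tests; if independent, the chance of at least one false positive is 1 − 0.95^12 = 46%.

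Power for an interaction as large as the overall effect, with independent strata, uses noncentrality 2.802 × √[f(1 − f)]: 29% at 50:50, 25% at 70:30 and 20% at 80:20. Shared site error cancels in the contrast, so at 50:50 the noncentrality becomes 2.802 / [2√(1 − s)]. That is 1.98 (51% power) at s = 0.5 and 3.13 (88%) at s = 0.8. An interaction half that size has noncentralities of 0.70, 0.99 and 1.57 at s = 0, 0.5 and 0.8, with power of about 11%, 17% and 35%.

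**4. Scale.** The planned link is logit, so an interaction term is a ratio of odds ratios. Take invented rates of 60% and 80% and a common odds ratio of 1.5. The odds go from 1.5 to 2.25 (69.2%) and from 4 to 6 (85.7%). The absolute gap falls from 20.0 to 16.5 points with no logit interaction at all. The logit term alone therefore does not measure a change in the absolute gap.

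**The case against.** The strongest reply is that the article claims little here. The subgroup work is exploratory, disparity is not a primary hypothesis, and the abstract's sentence on disparities is conditional. Sites were chosen for high proportions of underserved youth, so an overall gain at such sites could support that sentence without any difference in effect within sites. The article does not say that strata will be judged by separate p-values, and stratum estimates could be contrasted afterwards. It is also a condensed account, and detail on comparing strata may sit in a fuller document.

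Most of this stands and limits the point. A reader might infer that stratified fits cannot show a difference at all, that disparity reduction is a conclusion the trial has committed itself to, or that the strata are too small for stable fits. The documents support none of these. Estimates can be contrasted later, the disparity statement is conditional, and no stratum sizes are given. Nor can a single 50% be taken as the rate of misleading patterns in this design, because shared site error changes it.

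The reply does not remove the point. The article states a method for demographic factors in the sentence directly after it states a better suited one for site factors, so this is a stated choice and not an omitted detail. The exploratory label limits how strongly a result may be claimed, but does not supply the missing contrast.

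**Conclusion.** The point holds as a minor one. As written, the plan estimates no difference in intervention effect between demographic groups, while the article repeatedly connects the trial to disparities. The primary analysis is unaffected.

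The size depends on how strata are read. With equal true effects and 80% overall power, two equal strata disagree on significance about 50% of the time if independent and about 20-40% when half or more of the error is shared at site level. More strata give higher figures. These numbers rest on assumed stratum shares and an assumed shared-error fraction. The structural point, that no contrast is planned, rests on neither.

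**What to change.** In Data Analysis, change the sentence on stratified analyses as follows.

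- Add intervention-by-race/ethnicity, intervention-by-age and intervention-by-gender terms, one factor at a time, to the full-sample GLMM for each cascade outcome.
- Report the interaction estimates and the subgroup effects from that model with confidence intervals, together with the model-based change in the absolute gap between groups.
- Label all of this exploratory, keep stratum-specific fits descriptive, and base any statement on disparities on these contrasts.

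**Cost:** about 12 models (3 factors × 4 outcomes) and no new data, since the factors are already covariates and analysis is due to begin only in early 2026. Each test carries its own 5% error, so isolated positive results need caution. Interaction power is likely to be low (20-29% for an interaction as large as the overall effect under independence, and only about 11-35% for one half that size even allowing for shared error). The text should therefore say that a non-significant interaction is not evidence of equal benefit.

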## Results

As of May 2025, preparatory activities have been completed. These include finalization of the Connected for Wellness mobile app, IRB approvals, staff training, and recruitment of 20 participating sites (10 schools and 10 clinics randomized to cohorts). App deployment and participant recruitment are expected to begin between August 2025 and September 2025. App data collection and analysis of both app data and administrative data from the sites will begin in early 2026. Preliminary analyses are anticipated for October 2026. No results related to the study hypotheses are available at this time, but baseline engagement metrics and user demographics will be summarized once data are available. IRB approval was granted on July 1, 2025.

## Discussion

### Expected Findings

Innovative aspects of our clinical trial include the use of a mobile app codeveloped through participatory informatics integrating youth and caregiver priorities into its design to ensure that it addresses their specific needs. The app incorporates machine learning–driven, customizable features that offer personalized mental health resources focusing not only on mental health but also on addressing social determinants of health, such as housing and educational needs. By promoting local resources and providing tailored, real-time suggestions, the app helps bridge gaps in both mental health care and social services, ensuring that youth and caregivers can access the support they need in their everyday environments.

The growing body of evidence on mobile apps for mental health highlights their potential to improve access to care, engagement, and outcomes, particularly for underserved populations. While mobile health app technologies are increasingly recognized as scalable and accessible tools, their effectiveness is often dependent on personalization and relevance to the user’s context. Few studies have focused on participatory, co-design approaches tailored for youth and caregivers, which is where our study stands apart. By integrating machine learning, the app can dynamically adjust to the needs of each user, positioning it as an innovative solution in the field of mobile health.

Low-income populations, who often face barriers to accessing traditional health care [2], demonstrate high levels of cell phone and mobile internet use [43]. This provides a unique opportunity for mobile apps to address health care disparities. Research has shown that emergency departments increasingly serve as safety nets for underserved populations, especially for low-acuity conditions that could be managed in primary care settings. Mobile app tools designed to connect individuals with timely medical advice could reduce emergency department use, improving overall health care access [44]. While the potential exists, understanding the feasibility of underserved populations engaging with mobile apps to improve mental health care is essential [45]. A recent review of 36 trials conducted among youth found that, while mobile apps show promise in addressing issues such as depression, anxiety, and substance use, the evidence remains uncertain or limited [46]. Most of the studies included in the aforementioned review were small in scale, focused primarily on efficacy for youth already identified as at risk of depressive symptoms, and highlighted the need for larger trials to assess effectiveness and explore subgroup differences. Our study aims to address these gaps in scientific literature by testing a comprehensive, participatory, and machine learning–driven mobile app designed to improve wellness practices as a form of prevention while also improving service use outcomes for youth. This study places a strong emphasis on population health, embedding the intervention within school and primary care clinic settings.

### Limitations

The stepped-wedge design offers several advantages, including the ability to evaluate the intervention’s effectiveness while ensuring that all students in a high school or primary care clinic have the opportunity to access the wellness and prevention components of the app along with peer and family supports. It also allows for the assessment of temporal trends and the potential for learning or adaptation over time. However, this design also has limitations. The sequential implementation of the intervention may introduce biases such as those arising from differences in timing or external events affecting specific sites. Although the mobile app helps ensure fidelity by providing a standardized intervention across sites, the design still requires careful planning to manage logistical complexities and ensure consistency in implementation across diverse settings. Finally, variability in site readiness and capacity to implement the intervention highlights the need for robust support and ongoing monitoring of study sites. This includes tracking factors such as staff size, mental health service capacity, and the presence of existing peer-to-peer programs throughout the study.

### Conclusions

If successful, this study will demonstrate how mobile apps can serve as universal mental health and prevention tools, complementing existing behavioral health resources and community strategies such as peer support and family navigation programs. The mobile app–supported public health approach offers an equitable, scalable solution that has the potential reach and effectiveness to significantly improve public health outcomes and could reduce mental health care stigma among underserved communities.

## Appendix

Multimedia Appendix 1 Project Timeline for Stepped-wedge trial of the Connected for Wellness mobile app.

Multimedia Appendix 2 Peer-review report by ZRG1 MOSS-T (50) Center for Scientific Review Special Emphasis Panel RFA-RM-21-021: UNITE Transformative Research to Address Health Disparities and Advance Health Equity (U01), National Institute of Mental Health (National Institutes of Health, USA).

## Abbreviations

DSMB: data safety monitoring board
GLMM: generalized linear mixed model
HIPAA: Health Insurance Portability and Accountability Act
IRB: institutional review board
WHO-5: World Health Organization–Five Well-Being Index
